
### Measurement of outcomes at follow-up

Documentation of first ACHD visit will be done at 12 and 24 month chart review and will include potential barriers to ACHD clinic attendance. Regarding secondary outcomes 1–3, participants will complete the follow-up questionnaires at home, independent of their parent(s). Adolescents not completing the follow-up questionnaires will be contacted by mail, email, or text (depending on their preference) every two weeks for a total of three times, and then telephoned once, to be reminded. A $25 gift certificate will be provided to participants at each of the 1, 6, 12, and 18 month time points to acknowledge their time and commitment to questionnaire completion.

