**Fig. 2 Fig2:**
[figure not shown]
Individual participant timeline

Immediately prior to Session One, the RN will review the cardiology chart to become familiar with the cardiac history including CHD diagnoses, names and dates of cardiac surgical procedures and cardiac catheterizations, and current cardiac medications and doses. Session One (1 h) will emphasize education; Session Two (1.0–1.5 h) will emphasize self-management. Details of each session are summarized in Table 1.

**Table 1 Tab1:** Transition Intervention: summary of characteristics and content

Characteristic	Session 1: Emphasis on Education (Held at time of enrollment)	Session 2: Emphasis on Self-management (2 months post Session 1)
Aim	To inform participants about their heart condition	To motivate participants to self-manage and selfadvocate
Approach	Didactic/educational	Experiential/engaging
Role of nurse	Teacher	Facilitator
Mechanism of change	Cognitive/learning	Behavioral/applied action
Content	a) Introduction to transition/its importance	a) Discuss education-related goal set in Session 1
	b) Discussion of confidentiality, promote trust with RN	b) Discussion of “self-management” and its relevance to health
	c) Creation of MyHealth passport, including	c) View & discuss six 1-min videos illustrating interactions between a health care provider (HCP) & young adults with poor vs. strong assertiveness skills
	- name of cardiac condition	
	- previous cardiac interventions	
	- name and purpose of medications	
	d) Review cardiac anatomy (patient-specific)	d) View & discuss “Talking with your doctor” video; review GLADD approach (Give, Listen, Ask, Decide, Do)
	e) Discussion of potential future cardiac complications (patient-specific)	e) Role-play an interaction between a HCP & the participant who practices being assertive
	f) Review names & location of local ACHD cardiologists	f) Discuss SMART goal setting (Specific, Measurable, Attainable, Realistic, Timely)
	g) Introduction to relevant websites	g) Review booklet “When You’re 18”, take home
	h) Discussion of 3 scenarios addressing alcohol, smoking/street drugs, & sexuality/contraception	h) Visit website “Health Care Transitions”
	i) Introduce youth-oriented take-home written materials	i) Encourage email or text messages with RN. Questions posed within 7 days:
		1. “What helped you the most?”
		2. “What helped you the least?”
		3. “Do you have any questions for me?”
	j) Set one education-related goal for session 2	

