	k) Accompany participant to the ACHD clinic	
	l) Provide study email address; encourage emails or text messages with RN. Questions posed to participants within 7 days:	
	1. “Where is your MyHealth passport now?”	
	2. “Have you used your MyHealth passport or shown it to anyone?”	
	3. “Do you have any questions for me?”	

*ACHD* adult congenital heart disease; RN: registered nurse

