### Secondary outcomes

Given the complex, multidimensional nature of the transition process, transition interventions need to consider multiple outcomes, including cognitive factors (e.g. CHD knowledge) and self-management behaviours. Therefore, several secondary outcomes are proposed. All baseline questionnaires will be completed in the pediatric clinic, and prior to Session One for those in the intervention arm.Change in MyHeart scores between baseline, 1, 6, 12 and 18 months. The MyHeart scale consists of eight questions that assess participant’s knowledge of their cardiac condition. The MyHeart scale was developed for the CHAPTER 1 study, with a significant improvement in score observed at 1 and 6 months post intervention, compared to participants in the usual care group [16].Change in Transition Readiness Assessment Questionnaire (TRAQ) score between baseline, 1, 6, 12, and 18 months. The TRAQ is the most rigorous transition readiness scale for adolescents. Sawicki et al. identified behaviours relevant to transition, tested item reliability and validity, and then field tested the items with 194 youth with special healthcare needs [18]. Scores range from 0 to 5. Principal component factor analysis revealed two domains explaining 68 % of the total variance: self-management (16 items, mean score 3.01 ± 1.02) assessing skills such as filling prescriptions, understanding treatment side effects, and arranging medical follow-up visits; and self-advocacy (13 items, mean score 3.67 ± 0.77) assessing communication skills with the healthcare team, managing activities of daily living, and use of school and community resources. Internal consistency is high, with Cronbach’s alpha of 0.92 (Self-management) and 0.82 (Self-advocacy). A ceiling effect is unlikely given the mean scores noted above. The reading level is Grade 5.7 and this instrument takes ~5 min to complete. The 12 and 18 month assessments will provide longitudinal data on evolution of self-management and self-advocacy skills and will allow participants in the intervention group sufficient time to apply the skills gained (e.g., to independently book a physician appointment).Change in the Williams’ Scale between baseline, 1, 6, 12, and 18 months. The Williams’ scale is a measure of medical self-management and transition readiness among adolescents with special health care needs, having high internal consistency (Cronbach’s alpha 0.89) [17]. This consists of 21 Likert-scaled items and has a grade 4.9 reading level.Assessment of patient engagement via a cardiologist questionnaire. This questionnaire will be completed by the participant’s primary cardiologist at the first cardiology clinic visit (pediatric or adult site), after month 3 post enrollment. This questionnaire will help determine if those participants in the intervention group were more engaged with their cardiologist then those in the usual care group. The single-page questionnaire consists of six items and takes 1–2 min to complete.Incidence of cardiac re-intervention (surgery or interventional catheterization). Chart review at 12 and 24 months post enrollment will be done independently by two RNs who will be blinded to group allocation. This review will ascertain cardiac hospitalizations and invasive cardiac procedures (since study enrollment), confirm attendance at ACHD clinic, and identify new or progressive complications (e.g., endocarditis, heart failure, stroke, thrombosis, systemic or pulmonary emboli, arrhythmia requiring drug or procedural intervention, renal or hepatic failure) [2]. Discrepant adjudication will be resolved by a cardiologist team member.Frequency and content of verbal and written (email/text messaging/telephone) dialogue between intervention nurse and participant. The intervention RN will complete detailed post-intervention field notes after each session. Telephone communication (phone calls, text messages) and emails will be encouraged from participants at any time; all will be recorded verbatim and analyzed (see Quantitative data analysis below).

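### Follow-up MyHeart is completed at home with no stated from-memory condition while only the intervention arm holds a personalised passport, so arm differences may partly reflect look-up

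*Protocol article*

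**What the plan says.** The Secondary outcomes section lists MyHeart first. It is a knowledge measure: "The MyHeart scale consists of eight questions that assess participant’s knowledge of their cardiac condition". The outcome is "Change in MyHeart scores between baseline, 1, 6, 12 and 18 months". The items are not reproduced.

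The setting changes after baseline. Secondary outcomes: "All baseline questionnaires will be completed in the pediatric clinic, and prior to Session One for those in the intervention arm". Measurement of outcomes at follow-up, covering secondary outcomes 1 to 3: "participants will complete the follow-up questionnaires at home, independent of their parent(s".

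Table 1 describes what the intervention arm takes away from Session One, which is held at enrolment. The content includes "Creation of MyHealth passport, including" the name of the cardiac condition, previous cardiac interventions, and the name and purpose of medications. It also includes "Introduce youth-oriented take-home written materials" and an introduction to relevant websites. Within 7 days the nurse asks "Where is your MyHealth passport now" and "Have you used your MyHealth passport or shown it to anyone".

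The Usual care section mentions no passport. It does say that families are given written material about the child's CHD and, at the last pediatric visit, a package about the ACHD program. Care at the second site is described as similar.

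**The concern.** A knowledge test supports a claim about knowledge only if the answers come from memory, or if any aids are equally available in both arms. Here the test moves from the clinic to an unsupervised home setting just as one arm acquires a personal written record of facts in the tested domain. The one stated safeguard covers parents, a source that both arms have. It does not cover the passport, which only one arm has.

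What is at stake is how MyHeart is interpreted. A higher intervention mean could come from retained learning, from consulting the passport, or from both, and the data as planned could not separate them. Table 1 gives Session One a cognitive, learning-based mechanism of change, so the trial does intend to speak about learning. The planned mixed model of mean scores accounts for clustering and repeated measures. It cannot remove a difference in how the answers were obtained.

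**Working it through.** The plan states no figure for MyHeart: no SD, target difference or power. There is nothing to reproduce. The check has two parts.

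**1. The arms side by side at a follow-up MyHeart**

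| | Intervention | Usual care |
|---|---|---|
| Setting at baseline | clinic, before Session One | clinic |
| Setting at 1, 6, 12, 18 months | home | home |
| Stated condition at home | independent of parents | independent of parents |
| General written CHD information | yes (usual care is part of this arm) | yes |
| Personalised passport | yes, from enrolment | none described |
| Nurse prompt about the passport | within 7 days | none described |
| Take-home materials and websites from Session One | yes | none described |

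The Background section defines the comparison as intervention plus usual care against usual care alone. Usual-care material is therefore common to both arms, and the passport comes on top of it. Session One is at enrolment, so the passport exists before the 1-month test and every later one.

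**2. Illustration of size (every input below except the 60 per group and the 8 questions is an assumption)**

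Let q be the share of an arm that looks answers up and g the average number of items gained by those who do. With no true difference in knowledge:

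spurious difference = (q × g) in intervention − (q × g) in usual care

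With 60 per arm, an assumed SD of 1.5 to 2.0 items and no clustering, the standard error is SD × √(2/60), that is 0.274 to 0.365. The chance of a significant result favouring the intervention is Φ(difference / SE − 1.96), against 2.5% nominal in that direction.

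Usual-care look-up set to zero:

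- q = 10%, g = 1: 0.10 × 1 = 0.1 item (about 1% of the scale); chance about 5%.
- q = 25%, g = 2: 0.25 × 2 = 0.5 item (about 6%); chance 28% (SD 2.0) to 45% (SD 1.5).
- q = 50%, g = 2: 0.50 × 2 = 1.0 item (12.5%); chance 78% to 96%.

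Usual-care look-up allowed:

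- Intervention 25% gaining 2, usual care 10% gaining 2: 0.5 − 0.2 = 0.3 item (about 4%); chance 13% to 19%.
- Equal q × g in both arms: difference 0.

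The result runs from negligible to substantial depending on inputs that the document does not give. Clustering would widen the standard error and lower these chances somewhat.

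**The case against.** Four objections have weight.

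- **Usual care is not without written material.** This stands. A reader might infer that MyHeart is open-book in one arm only. The Usual care section does not support that: families there receive written CHD information, and any participant at home can search the web. The difference between arms is a personalised, prompted document added to a shared background.
- **The passport may not answer the questions.** This also stands. Calling it an answer sheet would be an inference, because the eight items are not shown and overlap with the passport fields cannot be checked. Both concern the participant's own cardiac condition, so some overlap is plausible, but no more can be said.
- **The direction is not certain.** This stands in part. Usual-care participants can look things up too, and if they know less they may gain more each time, which would pull the comparison towards no difference. A net bias favouring the intervention is the most plausible direction because the extra aid sits there, but it is not guaranteed. Nor is the bias zero only when nobody consults the passport. It is also zero if no item overlaps, if those who consult it already knew the answers, or if look-up balances across arms.
- **Completion instructions may be on the form or in the full protocol.** This is possible, and the point does not claim that no such instruction exists. It rests on what the article does fix: home completion, with one condition against help, directed at a source both arms share. The Potential limitations section lists threats to internal validity and does not mention this one.

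It could also be said that using the passport is part of the intervention's benefit. Being able to find one's cardiac facts is useful, but it is a different claim from knowing them, and MyHeart is presented as measuring knowledge.

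**Conclusion.** The point holds in a limited form. Between-arm differences in MyHeart at 1, 6, 12 and 18 months may partly reflect look-up, most plausibly in favour of the intervention, because only that arm has a personalised passport and no from-memory condition is stated. The size cannot be derived from the document. The range of 0.1 to 1.0 item of 8 rests entirely on assumed look-up rates, item gains and SDs, and shrinks with any usual-care look-up.

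A reader might go further and infer that the trial would report a false sustained gain in knowledge. The document does not support that: it would presume both the result and the amount of look-up.

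The consequence is confined to one secondary outcome. The primary outcome, excess time to ACHD care, comes from chart review and is untouched. This is a worthwhile, inexpensive improvement and does not put the trial's main conclusion in doubt.

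**What to change.** In Measurement of outcomes at follow-up, extend the condition about parents: for MyHeart, both arms answer from memory, without the passport, written materials, websites or help from anyone else. Put the same instruction on the form. If the form already carries it, one sentence in the protocol is enough.

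Add one yes/no item after MyHeart, in both arms at each follow-up, asking whether anything was looked up. Report the proportion answering yes by arm and time point. Keep the main intention-to-treat mixed model on all questionnaires, and add a pre-specified sensitivity analysis that treats questionnaires marked yes as not obtained from memory.

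The cost is one instruction, one item and one extra analysis, with no added visits or staff. Two limits remain. Compliance is self-reported, and the item is answered after randomisation, so excluding on it can unbalance the arms. The sensitivity analysis is therefore supportive only.

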### Transition intervention

The intervention will be conducted by one of two cardiology registered nurses (RNs) at each site (total 4 RNs) who are experienced working with teens. Youth will attend two one-on-one sessions with the same RN. Sessions will be youth-oriented, interactive, and engaging. Session One will occur immediately after a pediatric cardiology clinic visit to minimize study burden and to adhere with recommendations that transition interventions be delivered in clinical settings [21]. Individual sessions, in contrast to group sessions, allow the content to be patient-specific. Session Two will occur two months after Session One, in conjunction with another clinic appointment or as the sole purpose of a return visit. Individual participant flow through the study is illustrated in Fig. 2.

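### The two-weekly reminder rule can carry the 1-month questionnaire past Session Two, in the intervention arm only; a minor timing overlap that a tighter 1-month reminder calendar removes

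*Protocol article*

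**What the plan says.** Four statements in the protocol article bear on this.

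- **Sessions.** Table 1 places Session One at enrollment. The section Transition intervention adds: "Session Two will occur two months after Session One". It allows the second session to coincide with another clinic appointment or to be a visit of its own. On content: "Session One (1 h) will emphasize education; Session Two (1.0–1.5 h) will emphasize self-management".
- **Questionnaires.** The section Secondary outcomes lists "Change in MyHeart scores between baseline, 1, 6, 12 and 18 months" and "Change in Transition Readiness Assessment Questionnaire (TRAQ) score between baseline, 1, 6, 12, and 18 months", with the same time points for the Williams' scale. On baseline it says: "All baseline questionnaires will be completed in the pediatric clinic, and prior to Session One for those in the intervention arm".
- **Reminders.** The section Measurement of outcomes at follow-up says: "Regarding secondary outcomes 1–3, participants will complete the follow-up questionnaires at home". Non-responders are contacted "every two weeks for a total of three times, and then telephoned once, to be reminded". No time point has a rule of its own.
- **Analysis.** The section Quantitative data analysis compares mean scores between arms at the named time points with mixed models. The article does not say how a form returned well after its due date is classified.

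**The concern.** Only about one month separates the due date of the first follow-up form from Session Two. Three two-weekly reminders and a call can take longer than that. The article nowhere says that pursuit of the 1-month form ends when Session Two takes place.

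The overlap is one-sided. A usual-care participant who answers late has simply answered late. An intervention participant who answers equally late may by then have attended a second session, face to face with the study nurse, on the skills that TRAQ's self-management domain and the Williams' scale measure. MyHeart is less exposed, because it measures knowledge of the heart condition, which belongs mainly to Session One.

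Month 1 is the only questionnaire point between the two sessions; the next is month 6. If late forms are analysed as month-1 scores, that point mixes responses after one session with responses after two, and the mixture depends on who responds late. What is at stake is the clarity of one time point on three secondary scales.

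**Working it through.** The article gives no figure to reproduce here, so the check is calendar arithmetic on the stated schedules.

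**Inputs from the article**
- Session One: day 0 (enrollment).
- First follow-up form due: 1 month.
- Session Two: 2 months after Session One.
- Reminders: three, 14 days apart, then one telephone call.

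**Not stated, so varied**
- Length of a month: 28, 30.4 or 31 days.
- First reminder: on the due date, or 14 days after it.
- Gap from the third reminder to the call: 0, 7 or 14 days.

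Month 1 is taken from enrollment. This fits a baseline form completed before Session One and a usual-care arm that has no sessions. The participant timeline (Fig. 2) is not available to confirm it. If month 1 were counted from Session Two, the point would not arise.

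**Formulas**
- Day of reminder k = due day + start offset + 14 × (k − 1), for k = 1, 2, 3.
- Day of call = day of third reminder + gap.

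**Results for a 30.4-day month** (form due day 30.4, Session Two day 60.9)

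| First reminder | Reminder days | Reminders after Session Two | Call day (gap 0 / 7 / 14) | Call relative to Session Two (days) |
|---|---|---|---|---|
| 14 days after due date | 44.4, 58.4, 72.4 | 1 (by 11.6 days) | 72.4 / 79.4 / 86.4 | +11.6 / +18.6 / +25.6 |
| On due date | 30.4, 44.4, 58.4 | 0 | 58.4 / 65.4 / 72.4 | −2.4 / +4.6 / +11.6 |

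Months of 28 or 31 days give the same pattern. The whole sequence ends before Session Two only if the first reminder is sent on the due date and the call follows the third reminder at once. With a 28-day month, even that case lands on the day of Session Two (day 56).

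**Possible size.** If late forms count as month 1, then

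shift in the month-1 difference = (share of intervention forms completed after Session Two) × (added effect of Session Two).

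The article gives neither term. Purely as assumptions, take a late share of 10% to 30% (6 to 18 of 60 participants) and an added effect of 0.3 to 0.5 SD:
- low: 0.10 × 0.3 = 0.03 SD
- high: 0.30 × 0.5 = 0.15 SD

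For comparison, the standard error of a difference between two means with 60 per arm is √(1/60 + 1/60) = √(2/60) = 0.18 SD, before clustering, attrition or baseline adjustment. The assumed shift lies below one standard error throughout.

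**The case against.** The strongest case on the other side has five parts.

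- **Late-form handling may be defined elsewhere.** Visit windows usually sit in the full protocol or SAP, which is not shown. This stands: the missing window is no defect of the article, and it cannot be said that a form returned on day 75 will be analysed as month 1. What remains is that two schedules fixed in the article overlap.
- **The days rest on unstated choices.** This also stands. A reader might infer that two of the four contacts certainly follow Session Two. That holds only if the first reminder is sent two weeks after the due date; otherwise at most the call does. The actual day of Session Two may also move with clinic appointments.
- **No month-1 single-session contrast is planned.** Correct. A reader might infer that a comparison with CHAPTER 1 at one month is compromised. The article plans no such comparison and does not designate month 1 as a test of Session One. For self-management skills it stresses months 12 and 18.
- **Post-Session-Two scores still reflect the allocated intervention.** Correct under intention to treat. A reader might infer that early TRAQ and Williams' differences will be overstated. That needs Session Two to raise scores and late forms to be counted as month 1; the article establishes neither. The secure statement is that the timing of exposure at month 1 becomes mixed in one arm.
- **Discarding late forms has a cost.** It would remove late responders, who may differ from prompt ones. Closing the window at each participant's own Session Two could give the arms unequal windows. This stands and shapes the fix.

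**Conclusion.** The point holds as a minor one. With month 1 counted from enrollment, and on every reading but one narrow one, the reminder rule pursues the 1-month form up to or past Session Two: by the third reminder and the call if reminders start two weeks after the due date, or by the call alone if they start on it. Late intervention-arm forms, chiefly TRAQ and Williams', may then follow the self-management session, and usual care has nothing equivalent.

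The effect is confined to the month-1 contrast of three secondary scales, and within it to intervention participants who answer only after Session Two. Their number is unknown because no non-response rate is given. The 0.03 to 0.15 SD illustration rests wholly on assumed inputs and indicates only that the shift is probably small. The documents do not support reading this as a threat to the primary outcome, to months 6, 12 and 18, or to the trial's conclusions.

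**What to change.** For the 1-month form only, use a compressed reminder calendar, identical in both arms. For example, send weekly reminders at about days 37, 44 and 51 (30 + 7, + 14, + 21) and make the call by about day 55, so that all contacts end before Session Two is due at about day 60. Keep the two-weekly schedule for months 6, 12 and 18.

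Record the completion date of every form. Keep forms returned after Session Two. Add a sensitivity analysis of the month-1 contrast that sets aside forms completed after one common cut-off, about day 60, in both arms. A common calendar cut-off gives the arms equal windows.

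The cost is slightly more frequent reminders at one time point, a date field and one extra analysis. The number of contacts and the timing of the sessions do not change. Some overlap would remain where a participant answers late despite the tighter calendar, or attends Session Two early; the recorded dates would show how often.
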